### Other collected variables

#### Tracking of intervention activities

ESRD Network staff will monitor compliance with policies and procedures (*i.e*., forming a Patient and Family Advisory Committee for transplantation, participation in monthly webinars, submission of monthly patient-level facility-reported referral data, etc.) on an at least amonthly basis. Coalition partners, including Georgia Transplant Foundation, will monitor facility participation in the Peer Mentoring program by tracking requests for peer mentors and peer mentor activities within facilities. Georgia Transplant Foundation and transplant center partners will monitor facility staff participation in educational activities across the state, such as Trends in Transplant conferences and Explore Transplant events.

#### Patient and dialysis facility staff satisfaction with intervention activities

To examine feasibility of expanding the intervention outside of GA, the SEKTC members, with assistance from ESRD Network resources, will send an informal email survey (via survey monkey) to all facility project leadership in the study to evaluate the fidelity, reach, context, and sustainability of each intervention activity (target n = 134).

To examine the patient impact of the multicomponent interventions, a sample of patients within dialysis facilities will be surveyed on the relevance, knowledge, and readiness to pursue transplantation. Process evaluation data for both facilities and patients are described in Table 2.

**Table 2 Tab2:** **Process evaluation data for medical directors and ESRD patients within dialysis facilities**

Dimension	Process evaluation question	Measurement
**Dialysis Facilities**		
Fidelity	To what extent was the intervention implemented as planned?	Checklist of each component of the intervention activity
Reach	To what extent did the intervention encourage participation?	Number of staff engaged; number of patients participating in intervention activities
Context	What were barriers and facilitators to implementing the intervention activities?	Open ended item at the end of the form
Sustainability	Are you willing to continue the intervention components at your facility indefinitely?	Yes/No Discrete Response for each intervention activity
**ESRD Patients**		
Participation	What was your level of participation in intervention activities?	Discrete level of participation item for each component of the intervention activity
Relevance	To what extent was the information offered relevant to you?	Checklist of each component of the intervention activity
Knowledge	Did the intervention component increase your knowledge about transplant options?	Self-reported assessment for each intervention component
Readiness	To what extent did the intervention component change your readiness to pursue transplant?	Measure of transplant readiness for each intervention component

### Statistical analyses

Descriptive analyses of facility-level baseline variables (demographic, clinical characteristics and transplant access measures) will be compared and differences between study arms at baseline will be evaluated using either *t* tests or their non-parametric equivalents for continuous variables and chi-square test for categorical variables. Significant differences in baseline characteristics will be adjusted when assessing the overall intervention effect as described above.

To evaluate the effect of the intervention on improvement in transplant referral by study arm, we will calculate the difference in facility-level transplant referral rate from baseline to 12 months for each facility in the study. Analysis of covariance (ANCOVA) will be used to test for post-intervention mean differences in referral rates for the control and intervention group after adjusting for the baseline referral rates and facility characteristics that differed significantly across the two arms at baseline. For skewed outcomes, differences in the intervention and control groups will be evaluated using a non-parametric Wilcoxon rank sum test.

For our secondary outcome, AA vs. white racial disparity in transplant referral, we will examine whether (i) the proportion of AA patients referred for transplantation increased from baseline to 12 month follow up at the facility level and (ii) whether there is a differential effect in the intervention group compared to the control group over time, after adjusting for between facility heterogeneity. A mixed effects model will be used to test for differences in the proportion of AA patients referred between baseline and 12-month follow up in the two study arms respectively. Fixed main effects of (a): time (measured in months from baseline; baseline assumed month 0) (b): intervention status (control = 0, intervention = 1), and (c) their interaction on referral disparity, averaged across different subpopulation of facilities will be assessed. Facility level random effects (intercepts and slopes) will be considered to adjust for variations in the average time trend due to unmeasured confounding independent of the intervention. If the individual facility trajectories indicate a similar time trend (slope), a random intercept only model will be sufficient to account for between facility heterogeneity at baseline.

To examine the absolute increase of the intervention on AA ESRD patient referrals, patient-level logistic regression analysis will be performed with intervention status, race (AA versus whites) as primary independent variables and controlling for patient-level baseline characteristics. Because patients are clustered within facilities, we will adjust for the clustering effect. Interactions between intervention and race will be included to test for the differential intervention effects by race. For interpretation of findings, we will compare and contrast the standardized predicted referral rates by racial group within the intervention and control facilities, respectively.

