**Facility Demographic and Clinical Characteristics**				
# Patients per Facility, Mean, SD	46.0 ± 25.7	46.6 ± 25.5	45.4 ± 26.0	0.57
Number of Staff, Mean, SD	10.0 ± 7.4	10.1 ± 6.5	9.8 ± 8.1	0.48
For Profit, %	90.3	88.7	88.3	0.91
Average Age, Mean, SD	61.4 ± 5.9	61.2 ± 5.7	61.6 ± 6.1	0.76
% White	40.9	33.5	46.8	<0.001
% African American	56.5	65.4	49.0	<0.0001
% Uninsured	12.2	11.5	12.6	0.51
% Medicaid Only	9.1	11.0	8.5	0.01
% Unemployed	67.1	70.9	64.1	0.06
Time on Dialysis (Years), Mean, SD	4.9 ± 1.8	5.0 ± 1.21	4.8 ± 1.1	0.32
% Receiving No Access to Pre-ESRD Nephrology Care	27.3	26.0	28.3	0.28
% Not Informed of Transplant Options	2.8	3.1	2.4	0.28
% Diabetes	59.9	59.9	59.0	0.51
% Hypertensive	89.6	91.4	88.1	0.02
% AV Fistula	13.1	13.8	12.3	0.49
% of Incident Patients with AV Fistula	29.7	28.7	30.5	0.46
Average Count of Comorbidities, Mean, SD	3.0 ± 0.8	3.0 ± 0.8	2.9 ± 0.9	0.30
% ESA Prior to Dialysis	17.6	18.0	18.0	0.25
Standardized Mortality Ratio	1.06	1.07	1.05	0.41

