### Power and sample size calculations

Our sample size calculations are based upon our primary aim to improve access to kidney transplant referral and also feasibility and resource availability for intervention activities. To test the primary null hypothesis of no difference in referral proportions between the control and intervention groups, our sample size of 134 dialysis facilities (67 facilities in each arm), with an estimated 46 patients per facility, achieves 80% power to detect a moderate difference of 3.1% to 4.8% in referral proportions between the two groups at 5% significance level. The power calculation assumes a 14% crude referral proportion in the control group based on baseline referral data and an intra-cluster correlation coefficient (ICC) of 0.01 to 0.05, respectively, to account for between-facility variation.

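### The stated 80% power for a 3.1-point difference at ICC 0.01 treats every facility as having 46 patients; with the size spread in Table 1 the primary ANCOVA, for which no weights are stated, generally falls a few points short.

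*Protocol article*

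**What the plan says.** The Power and sample size calculations section bases the claim on "our sample size of 134 dialysis facilities (67 facilities in each arm), with an estimated 46 patients per facility". It says this design "achieves 80% power to detect a moderate difference of 3.1% to 4.8% in referral proportions between the two groups", "at 5% significance level", and that the calculation "assumes a 14% crude referral proportion in the control group". The ICC runs from 0.01 to 0.05, paired in order with the two differences. Facility size enters as one number, with no term for its variation and none for baseline adjustment.

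The Statistical analyses section names the primary test: "Analysis of covariance (ANCOVA) will be used to test for post-intervention mean differences in referral rates for the control and intervention group", adjusted for the baseline rate and for facility characteristics that differ between arms. Weights are neither specified nor excluded.

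Table 1 reports facility size for all Georgia facilities and then for the randomized pool: "Patients per Facility, Mean, SD 46.0 ± 25.7 46.6 ± 25.5". The section on target population and inclusion/exclusion criteria removed facilities with fewer than 25 patients aged 18-69 in 2012 (11 of 283).

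**The concern.** A referral rate from a small facility is noisier than one from a large facility. Averaged with equal weight, the noisy rates inflate the residual variance of the facility-level comparison. For facilities of 25 and 100 patients, the variance factor ICC + (1−ICC)/m is 0.0496 against 0.0199 at ICC 0.01, a ratio of 2.5. At ICC 0.05 it is 0.0880 against 0.0595, a ratio of 1.5. The loss should therefore appear mainly at the low-ICC end, which is where the protocol claims its smallest detectable difference.

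At stake is whether the trial can detect 3.1 points with the stated probability. A null result near that size would be read as more informative than it is. No bias or excess false-positive risk is alleged against the unweighted test.

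**Working it through.** **Inputs from the protocol.** 67 facilities per arm, 46 patients per facility, control proportion 0.14, ICC 0.01 or 0.05, alpha 0.05 (sidedness not stated; two-sided reproduces the figures). Facility size in the pool is 46.6 ± 25.5, so CV = 25.5/46.6 = 0.55.

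**Assumptions.** The Table 1 counts approximate the outcome denominators. The shape of the size distribution and the correlation between 2013 and 2014 rates are not given, so ranges are shown.

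**Step 1: reproduce the stated figures.** Effective patients per arm = 67×46/(1+45×ICC).
- ICC 0.01: 3082/1.45 = 2125.5. Power at 3.1 points is 79.7%; the detectable difference is 3.11 points.
- ICC 0.05: 3082/3.25 = 948.3. Power at 4.8 points is 80.6%; the detectable difference is 4.76 points.

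The printed figures are correct for equal facilities.

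**Step 2: the same design with the named test.** For an unweighted analysis of facility rates, the variance of one rate is p(1−p)×[ICC + (1−ICC)/h], where h is the harmonic mean facility size. Baseline adjustment multiplies this by (1−ρ²), where ρ is the correlation between observed baseline and 12-month rates. Power comes from a noncentral t with 131 df. With every facility at 46 and ρ = 0, power is 79.1% at 3.1 points and 80.2% at 4.8 points, close to Step 1.

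**Step 3: put in the size spread, at 3.1 points and ICC 0.01.** Observed rates cannot correlate more strongly than their reliability, ICC/[ICC + (1−ICC)/h], which bounds ρ.

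| Sizes (mean 46.6, SD 25.5) | h | Power, ρ = 0 | Largest ρ | Power there | ρ needed for 80% | Detectable difference, ρ = 0 |
|---|---|---|---|---|---|---|
| Gamma starting at 25 | 38.5 | 74.0% | 0.28 | 77.3% | 0.37 | 3.35 points |
| Lognormal, no floor at 25 | 35.9 | 71.8% | 0.27 | 74.9% | 0.42 | 3.44 points |
| Gamma, no floor at 25 | 32.9 | 69.0% | 0.25 | 71.8% | 0.48 | 3.55 points |

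For the first row, the variance factor is 0.01 + 0.99/38.46 = 0.0357, against 0.01 + 0.99/46 = 0.0315 with equal sizes. For all three shapes, the ρ needed for 80% exceeds the largest ρ possible.

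Beta-binomial simulations of the baseline-adjusted ANCOVA agree. Across their assumptions they span about 73% to 80% with sizes from 25, and about 68% to 73% without the floor.

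**Step 4: the other end, 4.8 points and ICC 0.05.** With ρ = 0, power is 78.0%, 77.0% and 75.7% for the three shapes. A ρ of 0.22 to 0.32 restores 80%, and up to 0.63 to 0.67 is possible.

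**Step 5: is equal weighting the whole cause?** No. Using the size CV in the design effect of a comparison pooled over patients gives 1 + [(1+0.55²)×46.6 − 1]×0.01 = 1.60 (unrounded CV 0.547), and power at 3.1 points of 76.3%. Weighting the ANCOVA by m/(1+(m−1)×ICC), with m the facility's number of patients, gave 77.4% in simulation (sizes from 25, no baseline correlation) and 79.6% with a correlation of 0.8 between true facility rates in the two years. The unweighted test gave 74.5% and 76.9% in the same settings. Across settings, the gain is about 1 to 3 points with the floor and about 6 to 7 without it (gamma shape). The weighted test's type I error stayed between 4% and 5%.

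**The case against.** The strongest case on the other side has four parts.

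- **Clustering is already handled.** The power calculation carries a cluster design effect. A reader might infer that it is a patient-level calculation that does not fit a facility-level test, and that this mismatch costs the power. The documents do not support that: with equal sizes the two agree within a point. What remains is that the design effect ignores variation in size.
- **Equal weighting is inferred from silence.** This is a condensed article, and weights may be set in an analysis plan not shown. That stands as a caution. It does not rescue the power figure, which omits size variation and falls short at 3.1 points in most settings even with weights.
- **The floor of 25 limits the loss.** This largely stands. Only 11 of 283 facilities (3.9%) fell below 25, so shapes with many smaller facilities are pessimistic. The floor refers to 2012 counts, however, whereas the outcome uses 2013 and 2014 denominators, and with the floor power is still generally under 80%.
- **A simple facility average is a legitimate target.** Randomization, delivery and the outcome definition are all by facility, and precision weights change what is estimated if the effect varies with size. This stands, and is why the equal-weight result should be kept alongside.

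**Conclusion.** The point holds for the 3.1-point, ICC 0.01 end of the claim. There the unweighted ANCOVA has roughly 73% to 80% power if sizes start at 25, and about 68% to 73% without that floor (the closed form reaches 75% for a lognormal shape in its most favourable case). Baseline adjustment generally does not close the gap, because facility rates at that ICC are too noisy to correlate strongly from year to year.

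The claim at 4.8 points and ICC 0.05 is generally safe given a moderate baseline correlation. A reader might conclude that the whole power statement fails, or that weighting alone would make it true. Neither follows: the shortfall lies mainly at one end, and the weighted test mostly stays a little under 80% there as well.

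The direction rests on the protocol's own figures. The exact size rests on the assumed size distribution and year-to-year correlation. The shortfall is modest, but it is cheap to correct.

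**What to change.** 1. In Power and sample size calculations, recompute the power or the detectable difference with the facility-size variation (CV 0.55 or, better, the actual list of facility sizes), and state the baseline correlation assumed. At ICC 0.01 and before any baseline gain, the unweighted detectable difference is about 3.3 to 3.4 points with the floor of 25, and up to about 3.6 without it. Attributing the existing figure to a weighted test would not be enough.
2. In Statistical analyses, specify a facility weight m/(1+(m−1)×ICC) for the baseline-adjusted ANCOVA, where m is the facility's number of patients under 70 and the ICC is one value fixed in advance within 0.01 to 0.05. Keep the equal-weight ANCOVA as a sensitivity analysis.

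The cost is one recalculation, a sentence of analysis text and a line of code, with no new data or facilities. The downside is that the estimate becomes a precision-weighted rather than a simple facility average; the sensitivity analysis shows whether that matters.

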### Target population, setting, and inclusion/exclusion criteria

Under the direction of Centers for Medicare & Medicaid Services (CMS), 18 regional ESRD Networks are responsible for the quality of care of patients with kidney disease in the US. ESRD Network 6 (GA, NC, and SC) has the largest ESRD patient population among the US ESRD Networks, servicing more than 600 dialysis facilities that treat ~40,000 patients. Approximately 47% of the dialysis facilities in ESRD Network 6 are located in GA, and these facilities treated more than 12,000 dialysis patients in 2012 [47]. The RaDIANT Community Study aims to target 134 outpatient dialysis facilities in GA, representing nearly half (47%) of all GA dialysis facilities.

All dialysis facilities within GA were considered for randomization of the intervention (n = 283). To ensure that each facility had a large enough population to detect a change in the main effect of disparity reduction, facilities with a 2012 population of <25 patients (18-69 years of age) were excluded from the potential pool of facilities (n = 11). The remaining facilities were selected in a step-wise selection process: 1) The presence of a racial disparity in transplant referral (n = 75), or 2) crude annual referral in the lowest 50th percentile (referral <0.06; n = 59) for the state. The presence of a racial disparity was based on a difference of the proportion of AA ESRD patients referred and the proportion of white ESRD patients referred. The remaining facilities selected had a calculated crude referral in the lower 50th percentile. The final pool of 134 facilities were randomized by generating a random number to either the intervention (n = 67) or control (n = 67) group (Figure 1). Dialysis facilities in the intervention group are not blinded to intervention activities; however, facilities selected as controls are blinded. Researchers are not blinded to dialysis facility allocation.

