### Outcome measures

The primary outcome of the RaDIANT Community Study is the change in facility-level transplant referral (for patients <70 years) from baseline. Baseline referral will be calculated as the average number of unique referrals in a dialysis facility over the 12-month period preceding the intervention (January-December 2013) divided by the total number of ESRD patients within the facility for that time period. Post-intervention crude referral will be measured as the average number of unique referrals generated from January-December 2014 divided by the total number of ESRD patients within the facility for the same 12 month intervention period. As described above, referral will be defined as the receipt of a referral by the transplant center. Patient-level transplant referral data with facility identifiers will be collected from all of the transplant centers in GA and aggregated to summarize the total number of referrals to any transplant center in the state divided by the total number of adult ESRD patients <70 years in the facility. If facility characteristics are not equally distributed at baseline between control and intervention groups, we will consider adjustment using a Standardized Transplantation Referral Ratio (STRR). The STRR will be defined as the total number of observed transplant referrals within a facility divided by the total number of expected referrals based on the state average and adjusting for relevant covariates, among patients aged 18–69 [similar to the Standardized Transplantation Ratio (STR) used by CMS] [1].

A secondary outcome of interest is the reduction in AA vs. white racial disparity in transplant referral. The reduction in racial disparity will be measured as the difference in the proportion of referrals among AA vs. whites. Furthermore, we will examine whether the total number of AA ESRD patients referred for transplant in the state of GA increased from baseline to 12 months to examine the absolute impact of the RaDIANT Community Study on improving access for AA ESRD patients in the state.

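### The primary test moves from baseline-adjusted ANCOVA to a covariate-free Wilcoxon test on an undefined skewness trigger, although ANCOVA does not need the switch

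*Protocol article*

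**What the plan says.** Under Outcome measures: "The primary outcome of the RaDIANT Community Study is the change in facility-level transplant referral (for patients <70 years) from baseline". Under Statistical analyses, "we will calculate the difference in facility-level transplant referral rate from baseline to 12 months for each facility in the study", and an ANCOVA then compares the arms' post-intervention mean rates "after adjusting for the baseline referral rates and facility characteristics that differed significantly across the two arms at baseline". The next sentence is the fallback: "For skewed outcomes, differences in the intervention and control groups will be evaluated using a non-parametric Wilcoxon rank sum test". Nothing in the section says how skew is judged, on which variable, or which variable the Wilcoxon test ranks.

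The trial's size is given under Power and sample size calculations as "our sample size of 134 dialysis facilities (67 facilities in each arm), with an estimated 46 patients per facility". The claim made there for this size is that it "achieves 80% power to detect a moderate difference of 3.1% to 4.8% in referral proportions between the two groups at 5% significance level". On the control rate: "The power calculation assumes a 14% crude referral proportion in the control group based on baseline referral data". The ICC is taken as 0.01 to 0.05. No correlation between baseline and follow-up rates appears anywhere in the article.

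**The concern.** This is a stated rule for the primary test, and it fixes that test badly in four ways.

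- The choice of test depends on the outcome data with no threshold, in a trial where the article says the researchers know the allocation.
- The variable is open. The primary outcome is a change, while the ANCOVA models the post-intervention rate. These two variables differ in shape, so two analysts could follow the text and run different primary tests.
- A two-sample rank-sum test takes no covariates. In that branch neither the baseline rate nor an imbalanced facility characteristic can be adjusted for, although the preceding sentences promise both.
- The power section is about a difference in proportions. The rank-sum test addresses whether one arm's facilities tend to rank higher, and by itself gives no difference in proportions.

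At stake are the pre-specification of the primary result and, depending on the variable ranked, a material part of the power.

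**Working it through.** **Inputs.** From the article: 67 facilities per arm, 46 patients each (Table 1: mean 46.6, SD 25.5; minimum 25), control proportion 14%, differences 3.1 and 4.8 points, ICC 0.01 and 0.05, alpha 5% (taken as two-sided). Assumed: correlation ρ of true facility rates between years, 0.3 to 0.8.

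**1. The plan's own figure.** Patients per arm: 67 × 46 = 3,082. Design effect 1 + 45 × ICC: 1.45 and 3.25. Effective n: 3,082/1.45 = 2,125.5 and 3,082/3.25 = 948.3. A two-proportion test gives 79.7% power for 14% vs 17.1% and 80.6% for 14% vs 18.8%; the detectable differences are 3.11 and 4.76 points. The stated figure reproduces. It takes no credit for baseline adjustment.

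**2. Normal-theory comparison.** The largest possible correlation of observed yearly rates, with a fully stable facility effect, is 46 × ICC/(1 + 45 × ICC): 0.46/1.45 = 0.317 and 2.3/3.25 = 0.708. The observed correlation is r = ρ × that limit. Fix the unadjusted comparison of 12-month rates at the plan's 80% (noncentrality 2.80). Then:

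- ANCOVA: Φ(2.80/√(1 − r²) − 1.96)
- change score: Φ(2.80/√(2(1 − r)) − 1.96)

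| ICC | ρ | r | ANCOVA | 12-month rate | Change |
|---|---|---|---|---|---|
| 0.01 | 0.3 | 0.095 | 80.4% | 80% | 54.9% |
| 0.01 | 0.8 | 0.254 | 82.5% | 80% | 63.1% |
| 0.05 | 0.3 | 0.212 | 81.8% | 80% | 60.7% |
| 0.05 | 0.6 | 0.425 | 87.2% | 80% | 74.3% |
| 0.05 | 0.8 | 0.566 | 92.5% | 80% | 85.3% |

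The loss against ANCOVA is 0.4 to 12.5 points on the 12-month rate and 7.2 to 25.5 on the change. For normal data, ranking costs about 2 points more (noncentrality × √0.955); for skewed data it can gain.

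**3. Simulation** (beta-binomial, 67 + 67 facilities, sizes as in Table 1, 14% control, 1,000 trials per row; Monte Carlo SE about √(0.8 × 0.2/1,000) = 1.3 points).

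| ICC, difference | ρ | ANCOVA | Wilcoxon, 12-month rate | Wilcoxon, change |
|---|---|---|---|---|
| 0.01, 3.1 | 0.3 | 75% | 77% | 52% |
| 0.05, 4.8 | 0.3 | 79% | 79% | 59% |
| 0.05, 4.8 | 0.6 | 84% | 80% | 73% |
| 0.05, 4.8 | 0.8 | 90% | 78% | 83% |

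A separate run put the loss at about 6 to 24 points for the change, and between a 3-point gain and a 7-point loss for 12-month rates. The largest loss on rates in this kind of run, at ρ = 0.8 and ICC 0.05, is about 11 points (12 from the rounded row above).

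The result for rates depends on how the effect acts. With equal sizes of 46 and an effect proportional to each facility's rate (1,500 trials, ICC 0.05), ANCOVA and Wilcoxon on rates had 78.7% and 67.9% at ρ = 0.5 (loss 10.8), 83.0% and 66.4% at ρ = 0.7 (loss 16.6), and 96.7% and 67.7% with fully stable facilities (loss 29.0). In that last setting Wilcoxon on the change had 94.4%.

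**4. Would the trigger fire?** A standard skewness test on control-arm 12-month rates at 14% rejected in about 35% of trials at ICC 0.01 and 79% at ICC 0.05. On the change, mean skewness was about zero and the test rejected in about 6 to 17%. At an assumed 6% mean, rates were flagged in 76% (ICC 0.01) and at least 99% (ICC 0.05).

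**5. Is the switch needed?** With no effect, plain ANCOVA rejected in 4.1 to 5.5% of trials across the runs, including settings more skewed than 14% implies.

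**The case against.** The strongest reply is that the power section never counted on baseline adjustment. The stated 80% is an unadjusted figure, so a rank test on 12-month rates gives up mainly an ANCOVA gain that was not claimed. That stands for rates: Wilcoxon had 77 to 80% in the main table. It does not rescue ranking the change, which had 52 to 59% at ρ = 0.3, nor rates under a proportional effect (66 to 68%).

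It can also be said that a skewness threshold and the reported estimate belong in a statistical analysis plan that is not shown. True of those details. The point concerns the rule that is stated: leaving an adjusted analysis for one that cannot adjust. The Standardized Transplantation Referral Ratio under Outcome measures could carry some covariate adjustment if it were ranked, but the analysis section does not say so.

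Three stronger readings are tempting and are not supported.

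- *Skew is near certain.* A reader might infer this from the selection rule "crude annual referral in the lowest 50th percentile (referral <0.06", which brought in 59 of the 134 facilities. That is a selection cutoff, not the pool's mean; the plan assumes 14%. At 14% and ICC 0.01 skew is found in only about a third of trials, and the change is close to symmetric.
- *The fallback always discards the baseline.* Ranking the change keeps it, as a raw difference instead of a regression adjustment.
- *The loss is 28 points.* That size needs a setting outside the plan, such as ranking the change at 6% plus 2.2 points (79.9% vs 51.6%), or 12-month rates with an observed correlation near 0.7, which at ICC 0.05 is the limit for fully stable facilities.

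**Conclusion.** The point holds in limited form. The article makes the primary test depend on an undefined trigger, and the alternative test cannot make the promised adjustment or test the powered difference in proportions. At the plan's 14%, with ρ assumed between 0.3 and 0.8, the cost relative to ANCOVA is about 6 to 24 points if the change is ranked. If 12-month rates are ranked, it runs from a small gain to about 7 to 11 points lost, and more if facility rates are almost fully stable or the effect is proportional to each facility's rate.

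The two rank tests fail in opposite places: the change when year-to-year correlation is low, the 12-month rate when it is high. ANCOVA was best or within about 3 points of best at 14% with ρ from 0.3 to 0.8. These losses are measured against ANCOVA and should not be subtracted from the stated 80%. With 67 facilities per arm, nothing here suggests that ANCOVA needs protection from this degree of skew.

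**What to change.** Name the baseline-adjusted ANCOVA of the 12-month referral rate as the single primary analysis whatever the distribution. Guard against non-normality with robust standard errors, or with a p-value from re-randomizing the 67/67 allocation using the same adjusted statistic. Report the adjusted difference in referral proportions with its confidence interval. Keep the Wilcoxon test as a sensitivity analysis and state which variable it ranks; ranking the residuals from a regression on baseline would retain the adjustment.

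The cost is a sentence or two in the analysis section and a few lines of code. Sample size and data collection are unchanged.

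### The Outcome measures and Statistical analyses sections do not agree on what is modelled for the racial-disparity outcome, and one stated response cannot show whether the AA–white gap narrowed

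*Protocol article*

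**What the plan says.** Outcome measures names the secondary outcome ("A secondary outcome of interest is the reduction in AA vs. white racial disparity in transplant referral") and its metric: "The reduction in racial disparity will be measured as the difference in the proportion of referrals among AA vs. whites". The facility selection rule under Target population uses the same kind of contrast, the proportion of AA patients referred set against the proportion of white patients referred.

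Statistical analyses opens the relevant paragraph by naming the AA versus white disparity. Its question (i) is whether "the proportion of AA patients referred for transplantation increased from baseline to 12 month follow up at the facility level". Question (ii) asks for a differential effect by arm over time and names no racial group. The model sentence reads: "A mixed effects model will be used to test for differences in the proportion of AA patients referred between baseline and 12-month follow up". The next sentence lists fixed effects of time, of intervention status, and "their interaction on referral disparity, averaged across different subpopulation of facilities will be assessed".

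The following paragraph adds a second model: "To examine the absolute increase of the intervention on AA ESRD patient referrals, patient-level logistic regression analysis will be performed". It has intervention status and race as main independent variables, adjusts for clustering, and states: "Interactions between intervention and race will be included to test for the differential intervention effects by race". Standardized predicted referral rates by race and arm are to be compared when interpreting the findings.

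**The concern.** A disparity is a contrast between two groups. A model whose response is the AA proportion, with no race term, estimates how AA referral changed. It carries no information on white referral.

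The intervention is delivered to whole facilities: staff education, facility action plans, monthly reporting, and materials for all patients. White referral may therefore rise as well. If it rises as much as AA referral, the gap is unchanged; if it rises more, the gap widens. The AA-only arm-by-time effect is positive in both cases. Reported under the disparity outcome, it could be read as reduced disparity when none occurred. Reducing disparity is the trial's stated secondary aim.

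Because the article describes the response in two ways in consecutive sentences, an analyst could follow either and claim to have kept to the plan.

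**Working it through.** **1. The plan's own figure.** The article gives a power figure for the primary outcome only. With 67 facilities per arm, 46 patients each, 14% in controls and a two-sided 5% level (two-sided is assumed), effective n per arm = 67 × 46 / (1 + 45 × ICC).
- ICC 0.01: 3,082 / 1.45 = 2,126. Power for a 3.1-point rise is 79.7%.
- ICC 0.05: 3,082 / 3.25 = 948. Power for a 4.8-point rise is 80.6%.

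The stated 80% reproduces, and the present point does not turn on it.

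**2. The three descriptions side by side.**
- Outcome measures: the response is the AA–white difference in proportions.
- Mixed model in Statistical analyses: the response is the AA proportion in the model sentence and referral disparity in the next. The terms are time, arm and time-by-arm; race is not among them.
- Logistic model in Statistical analyses: the response is patient-level referral, with arm, race and arm-by-race. No time term is stated, the formal test is on the odds scale, and the stated purpose is the increase in AA referrals.

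**3. What the AA-only response can show.** The article gives no race-specific rates, so these are assumed. Suppose that in the intervention arm AA referral goes from 10% to 14% and white referral from 14% to 19%, with no change in control facilities.
- AA-only arm-by-time effect: 14 − 10 = +4 points.
- Gap (white minus AA): 14 − 10 = 4 points before and 19 − 14 = 5 points after, so 1 point wider.

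**4. The AA-only result is blind to white referral.** Now take a follow-up comparison of arms, again with assumed rates: controls at AA 12% and white 18%, with AA 4.8 points higher under intervention. AA patients per facility are 46 × 65.4% = 30.1 (Table 1 share), so effective n per arm = 67 × 30.1 / (1 + 29.1 × ICC), or about 1,562 at ICC 0.01 and 821 at ICC 0.05.
- White also 4.8 points higher: the gap is 6.0 points in both arms.
- White 8.0 points higher: the gap is 6.0 points in controls and 9.2 under intervention.
- Power of the AA-only comparison is the same in both cases: about 97% at ICC 0.01 and 79% at ICC 0.05.

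**5. What the race-by-arm interaction adds.** For the two cases in step 4 the odds ratio in AA patients is 1.481. In white patients it is 1.345 (gap unchanged) or 1.601 (gap wider). The ratios of odds ratios are 1.481/1.345 = 1.10 and 1.481/1.601 = 0.93. The interaction separates the cases, but an unchanged absolute gap does not give a ratio of 1. For the rates in step 3 the odds ratios are 1.465 (AA) and 1.441 (white), a ratio of 1.017, although the absolute gap widened.

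**The case against.** The strongest reply is that the article does not confine itself to AA patients. The paragraph opens with the AA versus white disparity, question (ii) names no racial group, and the sentence after the model sentence puts the interaction on referral disparity. The logistic model includes race, an arm-by-race interaction and predicted rates by race and arm. Those rates are on the absolute scale and would show a wider gap. Because facilities are randomized, a follow-up contrast of race by arm is valid without a baseline term. The odds-scale disagreement in step 3 is also slight: a ratio of 1.017, with z about 0.11 even when clustering is ignored, would not support any claim.

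Much of this stands. A reader might infer that the plan models AA patients only, that white patients never enter, and that a widening gap would go unseen. The text does not support that. What the reply does not supply is a named test of the disparity as defined. The logistic model is assigned to another question, its formal test is on a different scale, and the predicted rates are offered only as an aid to interpretation.

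A reader might also infer that the random-intercept option ("a random intercept only model will be sufficient to account for between facility heterogeneity at baseline") inflates type I error. The article allows it only when facility trends look similar, poses the question at facility level, and gives no between-year correlation from which to size any inflation. That is a separate matter and forms no part of this point.

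**Conclusion.** The point holds as an inconsistency. The article defines the secondary outcome as a difference between races, states its model for one race, and then describes that model's response as disparity. Under the AA-only reading, a positive result does not answer the secondary aim. The illustration gives a 4-point AA gain alongside a gap that is 1 point wider.

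The race-specific rates are assumptions. They show that the two quantities can move in opposite directions, not that they will. The power figures in step 4 also assume that the primary outcome's ICC range applies to AA patients and that facilities are of average size. The primary ANCOVA and the sample size are untouched. An analysis plan that is not shown may settle the response, but the article's own sentences still conflict and should be reconciled.

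**What to change.** In Statistical analyses, name one disparity test that matches Outcome measures. The modelled quantity should be the AA-minus-white difference in referral proportion. It can be the facility-level response in the existing time-by-arm model, or it can be obtained from a race-by-arm-by-time term in a model of both races. In either case, take the test and confidence interval from the arm difference in the change of that quantity on the absolute scale. Report the AA-only model as a separate AA-referral outcome and do not describe it as disparity.

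No new data are needed. Race and referral dates are collected from the transplant centers, and race-specific referral proportions are already used for facility selection and feedback reports. The change is one of wording.

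The cost is precision. With about 30 AA and 15 white patients per facility (46 × 65.4% and 46 × 33.5%) and 14% referral in both, the binomial standard error for one facility is √(0.1204/30.1) = 6.3 points for the AA proportion. For the difference it is √(0.1204/30.1 + 0.1204/15.4) = 10.9 points, about 1.7 times as large. Facility effects common to both races cancel in the difference, so the overall penalty may be smaller. Where a facility has few or no white patients its own difference is unstable or undefined, which favors the model of both races over the facility-level response.
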